### Sample size and power analysis

For the primary outcome of smoking cessation, 182 participants per group is powered to detect an 11.6% difference [47] in the smoking abstinence rates between groups (with 80% power, alpha = 0.05 (two-tailed test) We will account for a 10% drop-out rate, and thus aim to recruit 203 per group (N = 812). Contextually, the smoking cessation rates we used for the sample size calculation (MT = 25.2%, usual care = 13.6%) represent a meaningful population health treatment effect doubling of the rate of successful quit attempts for the lowest SES group (11.4%; [9]).

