## Methods

The following protocol (version 5, September 9th 2022) follows SPIRIT guidelines for reporting protocols (see Additional file 1). In this four-arm parallel-group RCT of SRG, MT and MiCBT versus an active control (equal allocation ratio), we will deliver the interventions to small groups of smokers to maximise the potential cost-effectiveness. 6-months of these interventions will be followed by 6-months of online peer support and a further 6-month follow-up period. The control group will be directed to optional resources including counselling (Quitline) and information about pharmacological aid. We aim to: (a) test the efficacy of the three interventions (SRG, MT and MiCBT) for smoking cessation and (b) levels of resilience in low SES groups and how this changes during exposure to the interventions, (c) measure the cost-effectiveness and cost-utility of the interventions in low SES groups, and (d) undertake a process evaluation of the different interventions in low SES groups. We hypothesise the following:H1: The proportion of participants who report 14-day period abstinence from smoking at 6 months will be significantly higher for each intervention group compared to the control group.H2: Amongst participants that report 14-day period abstinence at 6 months, the proportion of participants who report 14-day period abstinence at 12 months will be significantly higher for each intervention group compared to the control group.H3: The proportion of participants who report 14-day period prevalence abstinence from smoking at 6 months post-trial (18 months from baseline) will be significantly higher for each intervention group compared to the control group.H4: Levels of resilience measured by the Connor-Davidson CD-25 [43] and ENRICHD Social Support Inventory [44] will be significantly higher for each intervention group compared to the control group at 6, 12 and 18 months post randomisation.H5: The interventions will improve smoking cessation and QALYs at a reasonable and acceptable incremental cost.

In addition, we pose the following research questions for the qualitative component of the study (that pertains to the process evaluation):RQ1: Have the different interventions been implemented and received as intended?RQ2: What are the barriers and facilitators associated with the first research question?RQ3: For whom, and in what circumstance were the interventions effective (and cost-effective) or not, and why?

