#### Analyses

All analyses will use Stata (version 17.0 [69]). This will be undertaken blinded to the participants’ group allocation. Mixed-effects modelling will be used to assess the effect of the interventions on primary and secondary outcomes. This approach accounts for the correlation of the data from repeat measures over time and reduces bias caused by missing data at one or more time points for each participant. In addition, we will develop prediction models to determine whether levels of internal and external resilience measured at baseline predict smoking cessation. As an exploratory analysis, we will also perform mediation analyses to determine the direct and indirect effects of the separate components of each intervention on the primary and secondary outcomes.

For outcomes assessed at a single time-point, we will assess the difference between the four groups at that time. For outcomes assessed at repeat time points, we will assess differences between the four groups at each time point, with adjustment for multiple comparisons. We will assess binary outcomes using mixed-effects logistic regression and continuous outcomes using linear mixed-effects regression. In repeated measures, we will treat time as a categorical variable, and the model will include fixed-effects for time and group. Subgroup analysis will be undertaken to test whether people with a critical level of resilience are more likely to stay quit than those that do not meet this level. The main analyses will be performed on a per-protocol basis. Our intention-to-treat population will be defined as all participants that were randomised and also completed the baseline survey. We will perform a sensitivity analysis on a modified intention-to-treat basis and impute missing data where possible. Where more than 10% of data are missing, we will also perform multiple imputation as a sensitivity analysis to account for possible bias in estimates caused by missing data. Missing smoking data will be presumed MNAR and analysed as continued smoking. Hypothesis testing will be performed using 2-tailed tests with a Type 1 error rate of alpha = 0.05, and 0.05/3 = 0.0167 when assessing each outcome across time to account for the repeated testing at 6, 12, and 18 months. We will make further adjustments for multiple comparisons (e.g., 3 comparisons with control) depending on each outcome.

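### The stated 80% power holds for one comparison at alpha 0.05; once the three primary comparisons with control are adjusted for, it is about 66–68% per comparison

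*Protocol article*

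**What the plan says.** The sample size section of the protocol article sizes the trial on one pair of rates, "MT = 25.2%, usual care = 13.6"%, "with 80% power, alpha = 0.05 (two-tailed test"). It states that "182 participants per group is powered to detect an 11.6% difference [47] in the smoking abstinence rates between groups (with 80% power"), then allows for loss: "We will account for a 10% drop-out rate, and thus aim to recruit 203 per group (N = 812"). It mentions no allowance for multiplicity.

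The Methods section describes a "four-arm parallel-group RCT of SRG, MT and MiCBT versus an active control (equal allocation ratio"). Its first hypothesis (H1) is that abstinence at 6 months is higher in each intervention group than in control, which makes three comparisons on the primary outcome. The primary outcome section fixes that outcome at 6 months (26 weeks).

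The Analyses section sets a two-tailed alpha of 0.05, and "0.05/3 = 0.0167 when assessing each outcome across time to account for the repeated testing at 6, 12, and 18 months". It then adds: "We will make further adjustments for multiple comparisons (e.g., 3 comparisons with control) depending on each outcome".

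**The concern.** The sample size calculation and the analysis rules use different significance levels. The calculation spends the whole 0.05 on one comparison. The analysis has three primary comparisons with control and expects to adjust for comparisons of just that kind. Any such adjustment lowers the power of each comparison, and the recruited number was not raised to make up for it.

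The stake is how the result is read. The control rate of 13.6% and the 25.2% target amount to nearly a doubling of quitting. If an arm with that effect misses the adjusted threshold, readers who believe the trial had 80% power will take the miss as stronger evidence against the intervention than it is. The threshold itself also matters: a p-value of 0.03 for one arm succeeds at 0.05 and fails at 0.0167.

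**Working it through.** **Inputs.** From the sample size section: rates 0.136 and 0.252, difference 0.116, two-sided alpha 0.05, power 80%, 182 evaluable per group, 10% loss, 203 recruited per group. From Methods: equal allocation and three comparisons with one shared control. From Analyses: the 0.05/3 split over time and the further adjustment for comparisons with control.

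**1. Reproduce the plan's figure.** Pooled-variance formula for two proportions, mean rate 0.194:

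n = [1.960·√(2·0.194·0.806) + 0.8416·√(0.252·0.748 + 0.136·0.864)]² / 0.116² = (1.096 + 0.466)² / 0.01346 = 181.2, rounded up to 182.

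182/0.9 = 202.2, rounded up to 203; 4 × 203 = 812. All three stated numbers reproduce exactly, for one comparison at 0.05.

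**2. Power per comparison at 182 per arm.** Power = Φ[(0.116 − z·s₀)/s₁], with z the two-sided critical value and

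- s₀ = √(2·0.194·0.806/182) = 0.04145
- s₁ = √[(0.252·0.748 + 0.136·0.864)/182] = 0.04100

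| Rule | Alpha per test | z | (0.116 − z·s₀)/s₁ | Power | Difference detectable at 80% |
|---|---|---|---|---|---|
| As sized, one comparison | 0.05 | 1.960 | 0.848 | 80.2% | 11.6 points |
| Dunnett, three arms | 0.0188 | 2.349 | 0.454 | 67.5% | 13.4 points |
| Bonferroni, three arms | 0.0167 | 2.394 | 0.409 | 65.9% | 13.6 points |
| Three arms and three times | 0.0056 | 2.773 | 0.026 | 51.0% | 15.5 points |

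The detectable differences hold control at 13.6% and solve the same formula for 80% power. Exact binomial calculation gives 66.2% for the Bonferroni row and 51.7% for the last row.

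**3. Holm.** Its power depends on how many arms work. Simulation at 182 per arm gives about 66% per comparison if one arm reaches 25.2% and the others equal control, and about 74% if all three reach 25.2%.

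**4. Leaving the three comparisons unadjusted.** Three tests at 0.05 that share one control of equal size have correlation 0.5 between their statistics. Numerical integration gives a 12.5% chance of at least one false positive. Exact binomial enumeration at a 13.6% rate gives 12.8% with 182 per arm and 12.3% with 203.

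**5. Sensitivity to the number analysed.** If all 203 per arm are analysed at the planned rates, power at 0.0167 is 71.5%. If the 10% lost are counted as smokers among 203, the rates shrink to 0.9·0.136 and 0.9·0.252, and power at 0.0167 is 64.8%.

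**6. What 80% would need.** At 0.0167 the formula in step 1 gives 242 evaluable per arm. 242/0.9 = 268.9, so 269 recruited per arm and 4 × 269 = 1,076 in total.

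**The case against.** The strongest reply is that the protocol makes no error. It states its alpha openly, and its numbers reproduce. The choice among Bonferroni, Holm and Dunnett, and of the outcomes each covers, can be left to a statistical analysis plan that is not shown. Separate interventions against a common control can also be argued to need no adjustment.

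Part of this stands. There is no arithmetic mistake, and leaving the procedure unnamed is not by itself a fault. But no analysis plan can make the 80% true per comparison once the three comparisons are adjusted for at the planned number. The protocol also does not argue that separate arms need no adjustment; it offers the three comparisons with control as its example of one.

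A reader might infer two stronger claims, which the document does not support:

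- **That the trial has 51% power.** This needs the 0.05/3 split over time to apply to the primary outcome as well. That outcome is fixed at 6 months, the Analyses section handles single-timepoint outcomes separately from repeated ones, and the Timepoints section lists later cessation assessments as additional to the primary. The split's three times match those of the resilience hypothesis (H4). The 12-month abstinence hypothesis (H2) is restricted to participants abstinent at 6 months, so H1 to H3 are not simply one outcome measured three times. The wording of the split, which covers each outcome, is loose enough to admit the reading, but 51% is its worst case.
- **That the plan carries a 12.5% family-wise error.** This arises only if the primary outcome is exempted from the protocol's own example of an adjustment. The protocol does not propose that.

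**Conclusion.** The point holds as a mismatch between two sections. The stated 80% power for 11.6 points applies to one comparison at 0.05. With the three primary comparisons adjusted for, as the Analyses section anticipates, power per comparison is about 66% (Bonferroni) to 68% (Dunnett). Under Holm it is about 66% if one arm works and about 74% if all three do. The difference detectable with 80% power is about 13.4 to 13.6 points.

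These figures assume 182 evaluable per arm, the planned rates, and independent participants, as in the protocol's own calculation. Varying the number analysed as in step 5 moves the Bonferroni figure between 64.8% and 71.5%, always short of 80%. The 51% and the 12.5% are conditional: the first on the time split also applying to the 6-month outcome, the second on the three comparisons going unadjusted.

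**What to change.** In the Analyses section, state that the three 6-month comparisons with control form the primary family, controlled at an overall two-sided 0.05 by Holm or Dunnett, and that the 0.05/3 split over time does not apply to the primary outcome.

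In the sample size section, replace the 80% claim in one of two ways:

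- the adjusted power: about 66–68% per comparison for 11.6 points, higher under Holm if several arms work; or
- the adjusted detectable difference: about 13.4–13.6 points with 80% power.

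N = 812 can stay, so no further participants are needed. The cost is a protocol amendment in wording and a less favourable stated power. It should be settled before the primary outcome is analysed, so that the threshold is not chosen with the results in view.

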### Measures

#### Primary outcome—smoking

The primary outcome is smoking cessation at the 6-month (or 26 week) timepoint. Smoking cessation is defined as 14 days of not smoking cigarettes, determined by two consecutive 7-day periods of self-reported smoking abstinence (“In the last seven days, have you smoked a cigarette, even a puff?”). Participants who meet this criterion at the time of the 6-month mark will be asked to self-administer a saliva test to detect the presence of cotinine (< 30 ng/mL), accurately reflecting abstinence for the preceding 3–4 days. Participants will be instructed to photograph the results and send them to the research team via SMS or email. The purpose of this one-time measurement is to biochemically verify the self-reported smoking cessation outcomes within the study. [48]

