**Methods:**

We plan a four-arm parallel 12-month RCT with a 6-month follow-up to test the efficacy of three group-based interventions each followed by peer support. Arm 1: mindfulness-integrated cognitive behavioural therapy; Arm 2: mindfulness training; Arm 3: setting realistic goals; Arm 4: active control group directed to quit services. All interventions will be administered online. Participants are adult smokers in Australia (N = 812) who have an average weekly household income less than $457AUD or receive welfare benefits. Group-based interventions will occur over 6 months, followed by 6 months of forum-based peer support. Primary outcome: self-reported 14-day period prevalence of smoking abstinence at 6 months, with remote biochemical verification of saliva cotinine (< 30 ng/mL). Secondary outcomes include: internal resilience (Connor-Davidson Resilience Scale-25); external resilience (ENRICHD social support tool); quality adjusted life years (EQ-5D-5L); self-efficacy for smoking abstinence (Smoking-Abstinence Self-Efficacy Questionnaire); motivation to quit smoking (Biener and Abrams Contemplation Ladder); nicotine dependence (Fagerstrom Test for Nicotine Dependency); equanimity (Equanimity Scale-16); stress (Perceived Stress Scale-10); goal assessment/attainment (Problems and Goals Assessment Scale).

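### The primary outcome rests on self-report with cotinine verification attached, and no rule says how a self-reported quitter with a positive or unreturned saliva test is classified

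*Protocol article*

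**What the plan says.** The section Primary outcome—smoking gives the definition: cessation means a fortnight without cigarettes, "determined by two consecutive 7-day periods of self-reported smoking abstinence". The saliva test follows as a second step, requested only from those who already satisfy the definition: "Participants who meet this criterion at the time of the 6-month mark will be asked to self-administer a saliva test". Return of the result depends on the participant: "Participants will be instructed to photograph the results and send them to the research team via SMS or email". The section closes with the test's role: "The purpose of this one-time measurement is to biochemically verify the self-reported smoking cessation outcomes within the study".

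The Methods paragraph of the abstract names the primary outcome as "self-reported 14-day period prevalence of smoking abstinence at 6 months, with remote biochemical verification of saliva cotinine (< 30 ng/mL". The first hypothesis, in the Methods section, speaks only of what participants report: "H1: The proportion of participants who report 14-day period abstinence from smoking at 6 months".

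Three other places bear on the point:
- The Analyses section treats missing smoking data as continued smoking. It does not say whether an unreturned saliva test is missing smoking data.
- The Phase 1 section offers every arm information on obtaining nicotine replacement. No section says how its use affects reading the cotinine result.
- The sample size section gives planning rates of 25.2% and 13.6% without saying whether they are self-reported or verified.

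**The concern.** The definition is complete before the saliva test is requested, and H1 counts people who report abstinence. Applied literally, a self-reported quitter stays a success whatever the test shows and whether or not it comes back. Yet the abstract and the stated purpose of the test suggest that verification is part of the outcome. Two statisticians working from this text could build different primary variables from the same data.

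The choice matters in this design. Intervention participants attend eight facilitated sessions and then receive peer support, while controls are directed to optional services. Participants therefore know their arm, and over-reporting of abstinence could differ between arms. A confirmed endpoint guards against that, but it depends on self-testing and on sending a photograph. The Discussion itself expects that online delivery may bring lower adherence and more drop-out, so incomplete return is foreseeable. The classification also carries into H2, which is restricted to those reporting abstinence at 6 months.

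**Working it through.** **1. The readings side by side, for a participant with two abstinent 7-day self-reports**

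| Saliva result | Definition and H1, read literally | Verification read as required | Missing-data rule |
|---|---|---|---|
| Returned, below 30 ng/mL | abstinent | abstinent | not relevant |
| Returned, 30 ng/mL or above | abstinent | not abstinent | does not apply; the result is not missing |
| Not returned | abstinent | not abstinent | smoking, but only if an unreturned test is missing smoking data, which is not stated |

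The readings differ in the second and third rows, and no sentence settles either.

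**2. The plan's own sample size**

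Inputs from the sample size section: 13.6% and 25.2%, two-sided alpha 0.05, 80% power, 10% drop-out. The mean rate is (0.136 + 0.252)/2 = 0.194.

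n = [1.960 × √(2 × 0.194 × 0.806) + 0.842 × √(0.136 × 0.864 + 0.252 × 0.748)]² / 0.116²
= (1.096 + 0.466)² / 0.01346 ≈ 181.2, so **182**.

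Power at 182 is 80.2%. Then 182/0.9 = 202.2, so 203 per group, and 4 × 203 = 812. All stated figures reproduce.

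**3. What a confirmed endpoint would do to power**

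Assumptions, none of them stated in the protocol:
- 13.6% and 25.2% are self-reported rates;
- the 10% who drop out are counted as smokers;
- a fraction r of self-reported quitters, equal in both arms, returns a result below the cut-off, and the rest are counted as smoking.

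The rates become 0.136 × 0.9 × r and 0.252 × 0.9 × r, with 203 per arm. Power = Φ[(d − 1.960 × SE₀)/SE₁], where d is the difference, SE₀ uses the pooled variance and SE₁ the separate variances.

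Example, r = 0.8: rates 0.0979 and 0.1814, d = 0.0835, SE₀ = 0.0344, SE₁ = 0.0342. (0.0835 − 0.0674)/0.0342 = 0.471, so power is 68.1%.

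| r | Control | Intervention | Power |
|---|---|---|---|
| 1.0 | 12.2% | 22.7% | 79.3% |
| 0.9 | 11.0% | 20.4% | 74.1% |
| 0.8 | 9.8% | 18.1% | 68.1% |
| 0.7 | 8.6% | 15.9% | 61.4% |

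The row r = 1.0 is the right comparator, because it already contains the drop-out handling.

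**4. Unequal confirmation (assumed), 182 per arm, no drop-out**

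- Control 80%, intervention 60%: 0.8 × 13.6% = 10.9% against 0.6 × 25.2% = 15.1%; power 22%.
- Control 60%, intervention 80%: 8.2% against 20.2%; power 91%.

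The observed difference can move either way, which is why return rates by arm are needed.

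**5. Over-reporting under a self-report endpoint with no true effect (assumed)**

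Take true abstinence of 13.6% in both arms, with 5% of intervention smokers and 2% of control smokers falsely reporting abstinence:
- intervention: 0.136 + 0.864 × 0.05 = 17.9%;
- control: 0.136 + 0.864 × 0.02 = 15.3%.

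That is a spurious difference of 2.6 percentage points. With 203 per arm it would reach significance in the intervention's favour in about 10% of trials. The 5% and 2% are illustrative only.

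**The case against.** The strongest reply is that nothing in the text is contradictory. The abstract and the outcome section each contain both elements, self-report and verification at the same cut-off. H1 can be taken as shorthand for the outcome as measured. This stands: a reader might infer that the abstract and Methods define opposing endpoints, but the documents do not support that.

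Nor do they say that the test has no effect on classification. That is one literal reading of the definition. A test described as verifying the outcome implies some role, but the role is not stated. Equally, the missing-data rule should not be stretched to make every unconfirmed quitter a smoker: it might reach an unreturned test, but cannot reach a positive one.

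A second reply is that derivation rules belong in an analysis plan or full protocol, neither of which is shown. This is fair for coding detail, and one cannot claim that no such document settles the matter. But whether reported or confirmed abstinence is the primary outcome is the definition itself. The article gives the question, cut-off and return route, and its literal rule counts a cotinine-positive participant as a success.

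A third reply is that the power loss depends on the planning rates being self-reported, and the protocol does not say so. If they are verified rates, 182 per group is unaffected by this point. The calculation also uses all 203 per arm, whereas the Analyses section makes the main analysis per-protocol. Both limits stand, and the figures are conditional.

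**Conclusion.** The point holds as a badly fixed primary endpoint. The text admits reported or cotinine-confirmed abstinence, and the literal version is the one exposed to differential over-reporting. Positive and unreturned tests have no stated classification, and self-reported quitters using nicotine replacement have no rule at all.

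It is not a numerical error. A reader might infer from the table that the trial is underpowered. The documents do not support that, because they do not say what kind of rate 13.6% and 25.2% are. Only if the rates are self-reported, with 10% drop-out counted as smoking and equal confirmation in both arms, does power fall from 79% to about 74%, 68% and 61% at 90%, 80% and 70% confirmation. Those confirmation levels are assumptions, as are the misreporting rates. The change should be made, since it uses a test already planned.

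**What to change.** 1. State one definition in the abstract, H1 and the primary outcome section: abstinence at 6 months requires both consecutive 7-day self-reports and a returned result below 30 ng/mL.
2. Count as not abstinent any self-reported quitter with no returned result, or with a positive result not explained by nicotine replacement use.
3. Write a rule for self-reported quitters using nicotine replacement. Cotinine is a nicotine metabolite, so the test alone can misclassify them. The rule requires that such use be known at the 6-month assessment.
4. Prespecify self-report alone as a sensitivity analysis, and report return rates by arm.
5. State whether the planning rates are self-reported or verified. If self-reported, restate the power for the expected confirmation rate.

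The cost is mainly wording, because the saliva test is already in the plan. Recording nicotine replacement use would be a small addition if it is not already collected. The downsides are a possibly lower stated power and some remaining misclassification of abstainers who use nicotine replacement.

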#### Phase 1 (months 0–6): group-based interventions

Participants allocated to interventions will attend eight 1-h group sessions online via Zoom over a 6-month period according to a prescribed ideal delivery schedule. Participants will be asked to provide approval these sessions to be recorded (so that they may provide data for analysis regarding intervention delivery, as described above). The facilitators running the interventions will have formal qualifications in CBT and will receive specialised training from experts in mindfulness training and setting realistic goals.

To ensure that all participants are encouraged to access the current best practice approach to smoking cessation, the Royal Australian College of General Practitioner’s [65] “Ask, Advise, Help'” model for smoking cessation will be offered to all participants from baseline, including active control group participants. This approach involves referral to behavioural counselling and provision of information on accessing Nicotine Replacement Therapy and stop-smoking medications where indicated. The behavioural counselling offered in the current study is via the Quitline service.

##### Arm 1

MiCBT is a four-stage therapeutic approach. [66] Therapy begins at the personal stage, with the internal promotion of experiential awareness and acceptance. The second stage introduces imaginary and in vivo exposure procedures, and the third stage extends mindfulness principles into interpersonal interactions. Stage four, the empathetic stage, involves developing ethical awareness and compassion, which is intended to help prevent relapse through counterconditioning. The approach is based on *Vipassana* (insight training) and the co-emergence model of reinforcement. This model proposes that operant behaviour is reinforced by the interoceptive feedback (i.e., conscious or unconscious bodily sensation) which co-emerges with self-referential cognitions, rather than the environmental consequences posited by Skinner. [67] Participants undergoing MiCBT will also be asked to complete 30—60 min of homework daily, including mindfulness practice twice daily and some readings. Homework will be guided by a smartphone application.

##### Arm 2

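### Cotinine below 30 ng/mL cannot verify abstinence from cigarettes in quitters using nicotine products, which every arm is told how to obtain, and no rule covers a positive test in a self-reported quitter

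*Protocol article*

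**What the plan says.** The section on the primary outcome sets the criterion in terms of cigarettes: "Smoking cessation is defined as 14 days of not smoking cigarettes". It is established by two consecutive 7-day self-reports, and the survey item asks only about cigarettes. Anyone who meets the criterion at 6 months "will be asked to self-administer a saliva test to detect the presence of cotinine (< 30 ng/mL"). The test is described as "accurately reflecting abstinence for the preceding 3–4 days", and its purpose is to "biochemically verify the self-reported smoking cessation outcomes within the study".

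The abstract joins the two parts and gives the primary outcome as "self-reported 14-day period prevalence of smoking abstinence at 6 months, with remote biochemical verification of saliva cotinine (< 30 ng/mL"). Hypothesis H1, in the Methods, speaks only of participants who report abstinence and does not mention verification.

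Under Phase 1, the general-practice cessation model includes "provision of information on accessing Nicotine Replacement Therapy and stop-smoking medications where indicated". This model "will be offered to all participants from baseline, including active control group participants". For the control arm the Methods say: "The control group will be directed to optional resources including counselling (Quitline) and information about pharmacological aid".

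**The concern.** The outcome and its verification measure different things. The outcome is about cigarettes. The marker is a breakdown product of nicotine, whatever its source. A person who has stopped cigarettes but still uses a patch, gum or e-cigarette meets the definition and can still test at 30 ng/mL or above. The trial itself points participants in every arm to one such product.

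The statement that the test accurately reflects abstinence is therefore not true of current nicotine users. The article states no exception for them and no rule for a self-reported quitter with a positive test. If the test decides, some people who meet the stated definition are counted as smokers. Equal use across arms would shrink the difference between arms and cost power. Unequal use would bias the comparison, in a direction set by which arm uses more.

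**Working it through.** **The plan's own figure.** Inputs from the sample size section: 13.6% (usual care), 25.2% (mindfulness training), two-sided alpha 0.05, power 80%. With the pooled-variance formula without continuity correction,

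n = [1.960·√(2·p̄·(1−p̄)) + 0.842·√(p₁(1−p₁) + p₂(1−p₂))]² / (p₂−p₁)², where p̄ = 0.194.

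The first term is 1.960 × √0.3127 = 1.096 and the second is 0.842 × √0.3060 = 0.466. Their sum squared, divided by 0.116² = 0.01346, rounds up to 182 per group. Power at 182 is 0.802. Allowing for 10% drop-out, 182/0.9 = 202.2, so 203 per group and 4 × 203 = 812. The stated sample size reproduces, and this point does not concern its arithmetic.

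**Illustration of misclassification.** Let q be the share of true cigarette quitters who fail the test because they used nicotine within its window. The documents give no value for q, so every value below is an assumption. The verified rate is the true rate × (1 − q). The table takes 13.6% and 25.2% as true rates before verification and 182 per group.

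| q control | q intervention | Control | Intervention | Gap (points) | Power |
|---|---|---|---|---|---|
| 0% | 0% | 13.6% | 25.2% | 11.6 | 80% |
| 10% | 10% | 12.2% | 22.7% | 10.4 | 75% |
| 20% | 20% | 10.9% | 20.2% | 9.3 | 69% |
| 30% | 30% | 9.5% | 17.6% | 8.1 | 62% |
| 30% | 10% | 9.5% | 22.7% | 13.2 | 93% |
| 10% | 30% | 12.2% | 17.6% | 5.4 | 30% |

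For example, with q = 30% in both arms, 0.136 × 0.7 = 0.0952 and 0.252 × 0.7 = 0.1764, a gap of 8.1 points. With equal failure, restoring 80% power would take 207, 238 or 279 per group at q = 10%, 20% or 30%.

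With no true effect (13.6% in both arms), shares of 30% and 10% give 0.136 × 0.7 = 9.5% and 0.136 × 0.9 = 12.2%. That is a spurious gap of 2.7 points in favour of whichever arm uses less nicotine, with about a 13% chance of a significant result in that direction, against a nominal 2.5%.

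**The case against.** The strongest reply is that the article nowhere says a positive test overrides self-report. Cessation is determined by self-report, the test is a separate one-off check, and H1 concerns reported abstinence. This stands in part. A reader might infer that true quitters are certain to be recoded as smokers, and the documents do not support that certainty. The abstract does, however, put verification into the primary outcome, so override is the natural reading. If self-report prevails instead, the role of a positive test is undefined.

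A second reply is that a nicotine-use item and a rule for discordant results may sit in the full protocol or analysis plan. That is possible. Table 1, which in any case leaves out the primary outcome, is not shown. A reader might take the cost-effectiveness section as proof that nicotine use goes unasked, but that section is about health care use and its costs. Absence of the item is therefore not established. What the article does fix is a cigarette-based outcome checked by a nicotine marker in all self-reported quitters.

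Third, a reader might infer that the error favours the interventions, because quit services and information on medication make up the control condition. The documents do not support a direction. The same offer goes to all arms from baseline, it is information and not the product, and intervention participants could use more.

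Fourth, only use within the 3–4 day window matters, so quitters who have come off nicotine products would pass. The rates of 25.2% and 13.6% may also be verified ones already, since they rest on a cited source that is not at hand. In that case the power loss shown would be partly double-counted. Both limits stand.

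**Conclusion.** The point holds as a mismatch between the stated outcome and its stated verification. Cotinine cannot distinguish a cigarette quitter with recent nicotine use from a smoker, and the trial tells every arm how to obtain nicotine replacement. If verification determines the outcome, such quitters would be misclassified.

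The numbers are illustrative. They assume that 10% to 30% of quitters fail the test for this reason and that the planning rates precede verification. On those terms, equal failure costs 1.2 to 3.5 points of the 11.6-point gap and leaves power between 75% and 62%. Unequal failure of 10% and 30% can inflate the gap to 13.2 points or shrink it to 5.4. They do not show that the trial is underpowered or biased towards any arm. Without nicotine use recorded close to the test, nobody could later tell which of these cases applied.

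**What to change.** 1. Add to the 6-month survey, if it is not already there, an item on use of nicotine replacement, e-cigarettes or other nicotine in the past 7 days.
2. State in advance how a positive test with self-reported abstinence is classified: cotinine of 30 ng/mL or more overrides self-report only in participants who report no nicotine product use.
3. Report a sensitivity analysis that counts all positive tests as smoking.
4. Report nicotine product use by arm.

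The cost is one or two survey items and a classification rule. The downside is that declared nicotine users rest on self-report alone. A smoker could avoid the check by declaring use, and if declared use differs by arm, so does the strictness of verification. The sensitivity analysis and the by-arm report expose this.

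Recruitment began in May 2021 and this version is dated September 2022, so some participants may already be past 6 months and would lack the item if it is new. For them, positive tests should be analysed both ways.
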